# Utilizing a low-carbohydrate/high-protein diet to improve metabolic health in individuals with spinal cord injury (DISH): study protocol for a randomized controlled trial

**DOI:** 10.1186/s13063-019-3520-3

**Published:** 2019-07-30

**Keywords:** Spinal cord injury, High-protein diet, Low-carbohydrate diet, Metabolic disease, Insulin sensitivity, Diabetes, Gut microbiome

## Abstract

**Background:**

Metabolic disorders (e.g., impaired glucose tolerance, insulin resistance, and type 2 diabetes) are more prevalent in people with spinal cord injury (SCI) than able-bodied individuals. Dietary modification is a more cost-effective treatment option than pharmacological therapies for reducing the risk of metabolic dysfunction. Lowering carbohydrate, increasing protein, and maintaining a proper dietary fat intake are expected to induce favorable adaptations in glucose control, body fat distribution, and the composition of the gut microbiome. However, dietary modification has not been rigorously investigated in people with SCI. The purpose of this study is to determine if an 8-week low-carbohydrate/high-protein (LC/HP) dietary intervention will show improvements in clinically important metrics of metabolic function, body composition, the composition of gut bacteria, and quality of life.

**Methods/design:**

We intend to recruit 100 participants with chronic traumatic SCI (3 years postinjury, C5–L2, American Spinal Injury Association impairment scale A–D, and aged 18–65 years) and insulin resistance, impaired glucose tolerance or untreated type 2 diabetes and randomly assign them to an 8-week LC/HP dietary intervention group or a control group. The daily LC/HP dietary intervention includes ~ 30% total energy as protein (1.6 g/kg per day) with a carbohydrate-to-protein ratio < 1.5 and fat intake set at ~ 30% of the total energy intake. The control group does not receive any dietary intervention and are continuing with their regular daily diets. Glucose tolerance, insulin sensitivity, β-cell function, body composition, gut microbiome composition, and quality of life measures are assessed at week 1, before starting the LC/HP dietary intervention, and at week 8, after completion of the LC/HP dietary intervention.

**Discussion:**

New information derived from this project will result in the development of a low-cost, simple, self-administered LC/HP dietary intervention for improving metabolic function in individuals with chronic SCI, improved understanding of the composition of gut bacteria in SCI, and how a LC/HP dietary intervention alters gut bacteria composition. In addition, this project will improve our understanding of the relationship between metabolic function and quality of life in individuals with long-standing SCI.

**Trial registration:**

ClinicalTrials.gov, NCT03207841. Registered on 5 June 2017.

**Electronic supplementary material:**

The online version of this article (10.1186/s13063-019-3520-3) contains supplementary material, which is available to authorized users.

## Background

More than 50% of individuals with spinal cord injury (SCI) are younger than 45 years of age [1, 2]. Therefore, more than half of individuals with newly acquired SCI have the potential to live a healthy and long life. While life expectancy has been increasing among individuals with SCI who survive the first year after injury, their life expectancy is still lower than that observed for the able-bodied US population [1, 3]. This is thought to result from secondary health conditions associated with neurological impairment, extreme physical inactivity, and deleterious body composition adaptations that ensue at the muscular [4], regional [5] and whole-body levels [6]. A significant decline in soft tissue lean mass and increased body fat mass has been repeatedly shown in the chronic stages of SCI [7, 8]. In addition, a positive relationship has been found between visceral adipose tissue cross-sectional area and fasting glucose and triglyceride levels [9]. Finally, completeness and higher level of injury have been shown to result in greater decline in lean mass compared with incomplete SCI [10, 11].

Secondary health conditions such as metabolic disorders (e.g., impaired glucose tolerance, insulin resistance, and type 2 diabetes) are more prevalent in people with SCI than able-bodied individuals [12, 13]. In fact, recent evidence from our laboratory shows a higher prevalence of insulin resistance among individuals with SCI (Fig. 1; ~ 80% in SCI patients versus ~ 50% in the able-bodied group, unpublished data). In addition, strong evidence [14–17] supports an SCI-specific threat for an accelerated trajectory of metabolic disorders, such that these health conditions occur at an earlier age in the SCI population than in able-bodied individuals, which often causes significant declines in functional independence, psychological health, and quality of life.

**Fig. 1 Fig1:**
[figure not shown]
Distribution of insulin sensitivity estimated by the Matsuda index based on data obtained from the oral glucose tolerance test for individuals with spinal cord injury (SCI) versus able-bodied individuals. A.U arbitrary units

In addition to physical inactivity and changes in body composition at the muscular, regional, and whole-body levels, the composition and function of gut microbiome exert a significant role in the pathogenesis of metabolic dysfunction [18]. Fecal transplant studies in both human and animal models suggested a cause-effect relationship between gut microbiome and the development of insulin resistance [19, 20]. The human gastrointestinal tract is colonized by 100 trillion bacteria, the composition and function of which is susceptible to a plethora of environmental (diet, medication use, physical activity, etc) and host genetic factors. In the case of SCI, the loss of central nervous system control over the gastrointestinal tract, neurological bowel dysfunction and altered colonic transit time are implicated in disruption of the gut microbiota composition (i.e., gut dysbiosis (GD)) [21–24] . GD developing shortly after SCI is accompanied by inflammation of the intestine [22, 23], increased intestinal permeability (leaky gut), and bacterial translocation from the gut into distal organs [23]. Microbial products found in the circulation promote systemic inflammation and the development of metabolic impairment [25, 26]. Importantly, diet seems to strongly influence the bacterial composition of the gut [27]. For example, high-fat, high-carbohydrate diets (a Western diet) have been shown to increase Gram-negative gut bacteria, which triggers an immune response resulting in systemic inflammation that precedes insulin resistance and diabetes in humans [28]. Individuals with SCI, like those of the general US population, consume far more fat and carbohydrate than recommended levels [29], which may affect their gut microbiome composition and increase their risk of metabolic dysfunction.

Dietary modification is an attractive countermeasure to the development of metabolic disorders in the SCI population. Lowering carbohydrate, increasing protein, and maintaining a proper dietary fat intake is expected to induce favorable adaptations in glucose control, fat distribution, and the composition of the gut microbiome. This improvement is thought to be due to the effects of protein on: 1) the sensation of feeling full after eating food despite similar or lower energy intake [30]; 2) contribution to storage of lean mass [31]; and 3) an insulin-sensitizing effect [32]. Our studies in SCI [33, 34] and other studies [35, 36] in able-bodied individuals with diabetes support this idea and demonstrate that it is possible to improve blood glucose control and insulin sensitivity in individuals with type 2 diabetes or impaired glucose tolerance by making relatively simple dietary adjustments, without the need for weight loss to improve glucose control. We have shown that increasing dietary protein from 15% to 30% of total food intake quantitatively increased insulin sensitivity from 4.6 (borderline insulin resistance) to 11.6 (insulin sensitive) in men with SCI who followed an 8-week low-carbohydrate/high-protein (LC/HP) dietary intervention (Fig. 2). Matsuda index values between four and five have been proposed as cut-off levels for insulin resistance among different able-bodied populations [37–40]. In addition, the LC/HP diet decreased homeostasis model assessment of insulin resistance (HOMA-IR) levels from 3.8 (insulin resistant) to 2.4 (insulin sensitive) [41]. These preliminary findings are both compelling and encouraging because extreme dieting (i.e., caloric deprivation) and weight loss were not required to achieve metabolic improvements in our study participants.

**Fig. 2 Fig2:**
[figure not shown]
Whole body insulin sensitivity estimated using the Matsuda index based on data obtained from the oral glucose tolerance test. The red line indicates the suggested cut-off value for insulin resistance. Higher values indicate greater insulin sensitivity (i.e., less insulin resistance). Values are shown as means ± standard deviations. A.U arbitrary units

The experimental data in the SCI population are limited; therefore, it is critical to acquire a more detailed understanding of the effects of a LC/HP diet on metabolic function, body composition, and composition of the gut microbiome. Therefore, in this clinical trial, our purpose is to test the central hypothesis that individuals with SCI and with insulin resistance, untreated type 2 diabetes or impaired glucose tolerance who follow a LC/HP diet will show improvements in clinically important metrics of metabolic function (glucose tolerance, insulin sensitivity, β-cell function), body composition (increase in lean mass and decrease in total and visceral fat mass), the composition of gut bacteria, and quality of life.


**Fig. 3 Fig3:**
[figure not shown]
SPIRIT schedule of study enrolment, interventions, and assessments. *Dietary recall is only performed for the control group. ^*&*^Physical activity recall assessment for people with spinal cord injury

**Fig. 4 Fig4:**
[figure not shown]
Study flow diagram. DXA: dual-energy x-ray absorptiometry, LC/HP: low-carbohydrate/high-protein, OGTT: oral glucose tolerance test, REE: resting energy expenditure, SCI: spinal cord injury, UAB: University of Alabama at Birmingham

The study population is expected to be representative for the demographics of the SCI patient population. Based on 2017 Spinal Cord Injury Facts and Figures, 81% of SCIs reported to the national database have occurred among males [2]. Therefore, we anticipate that among those who participate in this study, 81% will be male and 19% will be female. SCI is more common in non-Hispanic whites (63% non-Hispanic white, 22% non-Hispanic black, 11% Hispanic origin, 1% Native American, 2% Asian, and 1% other); therefore, we expect that more non-Hispanic whites, as compared with other racial or ethnic groups, will participate in this study. Children (aged < 18 years) are not eligible for this project.

### Adequacy of the potential participant pool

Using the most conservative estimate reported in existing prevalence studies [12, 43], at least 12% (12–22%) of individuals with chronic SCI develop Type 2 diabetes. Based on our clinical research experience in the SCI population, approximately 60% of individuals with chronic SCI develop impaired glucose tolerance and insulin resistance. A total of 355 individuals with SCI who have had a follow-up visit with UAB SCIMS since January 2011 continue to live within the Greater Birmingham Metropolitan Area (1-h drive or less to our research facilities at UAB). We are planning 4 years for enrollment (allocating months 1–6 to project start-up and the last 6 months to data analysis); thus, we expect to have access to a pool of 355 individuals with SCI over the planned enrollment period. Applying the prevalence of 12% for type 2 diabetes and 60% for impaired glucose tolerance or insulin resistance in the SCI population, we estimate to have access to a total of 256 local potential participants with SCI. Based on our power calculations (described below), a sample size of 60 (30 per group) is needed to see a statistically significant effect of our dietary intervention. The available estimated sample pool of 256 local individuals with SCI should be adequate for our enrollment needs.

### Power calculations

Power calculations were performed using nQuery Advisor + nTerim 3.0 and assumed a two-sided statistical test and a significance level of 5%. We obtained estimates of the standard deviation (SD) for two clinically important metrics of metabolic function: a Matsuda index (indicator of insulin sensitivity) of 3.8 units [33], and 2-h OGTT serum glucose levels of 16 mg/dL [44]. Given the dearth of publications related to the effects of diet composition on gut bacteria, we were unable to perform power calculations for gut bacteria composition; however, we have adequate power to detect statistically significant differences in primary metabolic outcomes.

As described in Fig. 4, we intend to recruit 100 participants (50 per group) for the study, taking into account an estimated final participation rate of 80% and an attrition rate of 20%. With a final sample size of 30 participants per group (LC/HP diet and control), and also assuming a two-group *t* test and the prior assumptions, we have 80% power to detect between-group differences of 2.8 units in the Matsuda index, and 11.8 mg/dL in 2-h OGTT serum glucose levels as being statistically significant. With this same sample size, and also assuming a paired *t* test and the prior assumptions, we have 80% power to detect within-group differences of 2.1 units in the Matsuda index and 8.5 mg/dL in 2-h OGTT serum glucose levels as being statistically significant. We believe that these estimates are conservative because we will be performing our primary statistical analyses for between-group and within-group comparisons simultaneously using statistical methods that are more sophisticated than those that are assumed here.

### Interventions/groups

Consistent with the interest of the National Institute on Disability, Independent Living, and Rehabilitation Research (NIDILRR) in participatory action research, the first phase of the study involves participants in the personalization of their own menu plans consistent with the parameters of the LC/HP diet. In the second phase of the study, the personalized menus are tested in a randomized controlled fashion in individuals with SCI with insulin resistance, untreated type 2 diabetes, or impaired glucose tolerance.

#### LC/HP diet group

All LC/HP participants meet with our registered study dietitian to discuss their food- and nutrition-related history. Food-related history includes a participant’s usual dietary patterns (measured by three 24-h dietary recalls), favorite foods, any food allergies/intolerances, any difficulties with eating (limited hand function) or chewing or swallowing, and any nutritional concerns. The next step includes planning a personalized menu that is consistent with the LC/HP diet parameters (for the LC/HP diet group) based on participant-specific requirements identified during the meeting with the registered dietitian. During the first 2 weeks, participants try a six-day-roating menu and decide if they want to change/substitute any food item. The study dietician makes suggested changes at the beginning of the third week and the diet plan including six different menus remains the same for the rest of the study. The daily LC/HP diet includes ~ 30% total energy as protein (1.6 g/kg per day) with a carbohydrate-to-protein ratio < 1.5 and fat intake set at ~ 30% of the total energy intake. These dietary parameters are designed to fall within the Acceptable Macronutrient Distribution Range established by the Institute of Medicine [45]. The LC/HP dietary intervention meets the recommended daily intake for fiber, vitamins, and minerals for adults aged 18–60 years. Dietary fat sources focus on monounsaturated and polyunsaturated fats, e.g., plant oils and nuts; dietary carbohydrate sources emphasize whole grains, fruits, vegetables, and legumes; and dietary protein sources include lean meats, fish, chicken, eggs, and nonfat dairy foods, e.g., fat-free milk and low-fat cheese, consistent with American Diabetes Association and Institute of Medicine guidelines. Participants in the LC/HP can consume water, diet drinks, crystal light, and unsweetened tea/coffee without any cream, milk, or sugar. Two cheat meals have been incorporated into the diet plan. Participants can consume one "cheat meal" of their choice at weeks 3 (after the final menu is decided) and 6 (2 weeks before final testing). "Cheat day" food and drink consumption is recorded by our study team and included in our analysis.

All LC/HP meals are provided by the UAB CCTS Bionutrition Unit and are delivered to participants’ homes weekly. Every delivery includes breakfast, lunch, dinner, and snacks for 7 days (a 1-day sample menu is shown in Additional file 2: Table S1). Once a week during the study, participants are weighed at their home with a portable wheelchair scale (Health O Meter 2400KL, 800 lbs. capacity) to ensure weight stability. If weight changes exceed 2 kg from baseline, calorie modification is prescribed to maintain each participant’s weight.

The overall energy/calorie needs of each participant is determined according to resting energy expenditure (REE), assessed via indirect calorimetry and multiplied by an activity factor. The Physical Activity Recall Assessment for People with Spinal Cord Injury (PARA-SCI) [46] is used to determine physical activity level and an appropriate activity factor (for estimation of calorie needs) for each subject. The PARA-SCI is an interviewer-administered recall questionnaire tailored exclusively to people with SCI who use a wheelchair as their primary mode of locomotion. PARA-SCI is as reliable as measures that have been used in large-scale epidemiological studies in the general population [47]. Physical activity levels may be different among groups (control and intervention) during the course of the study, which may mix in with the effects of diet and distort the true relationship of the intervention to outcomes in the intervention group. Therefore, we measure each participant’s physical activity levels via PARA-SCI [46] and physical activity levels will be treated as a potential confounder in our statistical analyses.

#### Resting energy expenditure (REE)

REE is measured at baseline (week 1) after a 12-h fast. Measurements are performed in a quiet and softly lit room. Temperature is maintained between 22 °C and 24 °C. Participants lay supine on a comfortable bed, with the head enclosed in a Plexiglas canopy. After resting for 15 min, REE is measured for 30 min with a computerized, open-circuit, indirect calorimetry system with a ventilated canopy (Vmax ENCORE 29 N Systems, SensorMedics Corporation, Yorba Linda, CA). The last 20 min of measurement is used for analysis. O_2_ uptake and CO_2_ production is measured continuously and values are averaged at 1-min intervals. REE is calculated from the O_2_ and CO_2_ data.

#### Safety of the LC/HP dietary intervention

Administering a LC/HP diet for a relatively short period of time (8 weeks) is not expected to produce any significant side effects. There have been no reported adverse side effects of this diet in long-term or short-term clinical trials in healthy individuals or patients with diabetes [48–50]. In fact, studies involving administration of a LC/HP diet for a relatively longer period of time (8–16 weeks) in obese patients and/or patients with diabetes have shown improvements in metabolic and cardiovascular disease markers (visceral fat, blood glucose, and insulin levels) [51, 52].

#### Control group

The control group does not receive any dietary intervention and are continuing with their regular daily diets; however, initial meetings with a registered dietician are required to gather information about their food- and nutrition-related history and to identify any control group participants who are already committed to a LC/HP diet. Individuals who are already following a LC/HP diet plan are not eligible to participate. Participants in the control group complete three 24-h food recalls (on two weekdays and one day at the weekend) three times (at weeks 1, 4 and 8) during the course of the study to gather dietary information including dietary intake and/or particular aspects of the diet. Participants are asked to recall foods and beverages they consumed in the 24 h prior to the interview. Three 24-h food recalls appear optimal for estimating energy intake [55, 56].

### Outcome measures and analysis

#### Primary outcomes

The primary outcomes are as follows: 1) metabolic function (glucose tolerance, insulin sensitivity, β-cell function and lipid profile); 2) body composition (total fat mass, total lean mass and visceral fat mass)l; and 3) gut microbiome (composition of gut bacteria).

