### Statistical analysis

All data analyses will be carried out using data from participants that complete the study intervention. Descriptive statistics will be calculated for all study parameters of interest. Analyses for all aims include comparisons of means of outcome measures, which include the Matsuda index (insulin sensitivity), 2-h OGTT serum glucose levels (glucose tolerance), β-cell function, total cholesterol, TG, LDL-C, and HDL-C, total lean mass, total fat mass, visceral fat mass, and composition of gut bacteria between the two groups (LC/HP diet and control diet) as well as comparisons within each group of the changes from the baseline visit to the week 8 visit. The primary method of analysis is mixed models repeated measures analyses, such as repeated measures analysis of covariance. An appropriate structure for the covariance matrix (e.g., the unstructured covariance matrix) will be selected for these models using the final data. This method allows us to compare changes over time (8 weeks) and differences between groups simultaneously. Potential confounders, such as age, gender, injury level, time since injury, and levels of physical activity, will be accounted for in these analyses. Overall adjusted comparisons between groups at baseline will be performed using the two-group *t* test, and overall unadjusted comparisons of the change from the baseline visit to the week 8 visit is performed using the paired *t* test. If assumptions of normality of distribution for the above tests are not tenable, variables may be log10 transformed prior to analysis or appropriate nonparametric tests such as the Wilcoxon rank-sum and signed-rank tests may be used. Generalized linear model techniques, such as regression analyses and mixed models repeated measures analyses, will be used to determine how changes in composition of gut bacteria are associated with improvements in metabolic function, or how improvements in metabolic function are related to improvements in quality of life. Secondary analysis of participants who have type 2 diabetes or glucose intolerance will be performed if the numbers of participants with these conditions differ greatly between the study groups. If we have missing data at study completion, we will not perform multiple imputation or apply the last observation carried forward method; instead, we will perform a secondary analysis of participants who completed the study versus participants who did not complete the study and determine if these two groups differ in any substantial way. Statistical tests will be two-sided and performed using a 5% significance level. SAS software, version 9.4 or later, will be used to conduct the statistical analyses.

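### Eleven unranked primary measures are tested at 5%, only two of them powered, and no rule says which result decides the trial

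*Protocol article*

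**What the plan says.** The Primary outcomes section names three domains: "The primary outcomes are as follows: 1) metabolic function (glucose tolerance, insulin sensitivity, β-cell function and lipid profile", then "2) body composition (total fat mass, total lean mass and visceral fat mass", then "3) gut microbiome (composition of gut bacteria". It gives no order of importance.

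The Statistical analysis section turns these into measures for comparison, "which include the Matsuda index (insulin sensitivity), 2-h OGTT serum glucose levels (glucose tolerance", and continues with "β-cell function, total cholesterol, TG, LDL-C, and HDL-C, total lean mass, total fat mass, visceral fat mass, and composition of gut bacteria". That makes seven metabolic measures, three of body composition and one for gut bacteria: 11 in all. The groups are compared with each other, "as well as comparisons within each group of the changes from the baseline visit to the week 8 visit". The level is the same throughout: "Statistical tests will be two-sided and performed using a 5% significance level".

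The Power calculations section covers the Matsuda index (SD 3.8 units) and 2-h OGTT glucose (SD 16 mg/dL), each at the full two-sided 5%. On the third domain it says "we were unable to perform power calculations for gut bacteria composition". It gives no figure for β-cell function, any lipid or any body composition measure. It also describes the primary analyses as making between-group and within-group comparisons together.

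**The concern.** A reader of the final report would need to know which result decides whether the diet worked, and the article does not say. Any of 11 measures could be presented as a primary success once the data are seen. So could a within-group change, since the primary analyses are said to include those. The Discussion expects the trial to demonstrate the efficacy of the diet, so the error rate behind a claimed success matters.

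The sample size does not fit the primary set either. It was derived for two measures, each with the whole 5% to itself, and nine of the 11 measures carry primary status with no power calculation. Gut composition is called primary in the same article that says it could not be powered.

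**Working it through.** **1. The plan's own power figure.** Inputs from Power calculations: 30 per group, two-group t test, two-sided 5%, SDs 3.8 and 16. The noncentrality is (difference/SD) × √(30/2), with 58 degrees of freedom.
- Matsuda index: 2.8/3.8 = 0.737, power 80.1%. The difference detectable with 80% power is 2.80 units.
- 2-h glucose: 11.8/16 = 0.7375, power 80.2%. The detectable difference is 11.77 mg/dL.

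Both stated figures reproduce, with the full 5% spent on each measure.

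**2. Count.** Matsuda index, 2-h glucose and β-cell function (3), four lipids (7), lean, fat and visceral fat mass (10), gut composition counted once (11). Powered: 2. Unpowered: 11 − 2 = 9, which takes in two whole domains.

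**3. Between-group tests only.** Under the global null with independent tests, the chance of at least one false positive is 1 − 0.95^11 = 1 − 0.569 = 43.1%. For jointly normal two-sided tests this is a ceiling whatever the correlations (Šidák's inequality).

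The article gives no correlations, so a common value is assumed. Each test statistic is √ρ × (shared normal) + √(1 − ρ) × (own normal), rejected beyond ±1.96.

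**4. Adding within-group tests.** There are then 3 × 11 = 33 tests, but they are not independent. If A and B are the standardised changes in the two arms, with equal variances, the between-group statistic is (A − B)/√2. This was simulated with no change in either arm.

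| Assumed correlation between measures | 11 between-group tests | Between-group plus within each arm |
|---|---|---|
| 0 | 43% | 74% |
| 0.3 | 37% | 67% |
| 0.5 | 30% | 57% |
| 0.7 | 22% | 44% |

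**5. Could an adjustment be added later without cost?** Power for 2.8 Matsuda units at 30 per group after a Bonferroni split:

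| Split over | Level per test | Power | Per group for 80% |
|---|---|---|---|
| 1 | 0.05 | 80% | 30 |
| 2 powered endpoints | 0.025 | 71% | 37 |
| 3 domains | 0.0167 | 65% | 41 |
| 11 measures | 0.0045 | 47% | 52 |

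No part of the 5% was held back for a correction of this kind. A fixed sequence leaves the first row intact.

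**The case against.** The strongest reply is that a journal article condenses the full plan, and an analysis plan not shown could contain a hierarchy or a correction. That is fair as far as it goes: the article does not rule out adjustment. But the point rests on what the article does fix, namely an unranked primary set, a 5% level for the tests, and a sample size with no allowance for sharing that 5%. Step 5 shows that a later Bonferroni correction would break the stated 80% power.

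A second reply is that independence is unrealistic. LDL-C is calculated from three other listed lipids, the Matsuda index and 2-h glucose come from the same test, and visceral fat is part of total fat. This stands, and it is why 43% is given as a ceiling. Counting only results that favour the diet lowers that ceiling to 1 − 0.975^11 = 24%, still almost five times 5%.

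Several stronger readings are tempting, but the article does not support them:
- A reader might infer that a false primary success is more likely than not. The between-group figures are all below one half.
- Treating all 33 tests as independent gives 1 − 0.95^33 = 82%. That ignores that each between-group contrast is built from the two within-group changes. The higher within-group figures also need a stricter null, with no change over time in either arm, and a change among controls is not in itself a false claim about the diet.
- A reader might count a separate 5% test for every bacterial taxon. The gut bacteria section says the organisms left after filtering are compared. It does not say how they are tested or how many there are.
- HOMA-IR is calculated but is not in the analysis list, so it is not counted as a further primary test.

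**Conclusion.** The concern holds. The plan names three unranked primary domains with 11 listed measures, tests at 5%, states no success rule, and powers two measures. The chance of at least one false between-group primary finding is at most about 43%, and about 22% to 37% over assumed correlations of 0.7 down to 0.3. It becomes about 44% to 74% if within-group tests count as primary evidence, assuming no change in either arm and equal variances.

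These figures assume the global null, approximately normal test statistics and gut composition counted as one test. The correlations are assumptions. The facts about ranking, level and power come directly from the article. A reader might take gut composition to be the only unpowered domain because the text admits it; body composition has no power calculation either.

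**What to change.** Amend the protocol before any outcome analysis:
1. Name one already powered endpoint as the sole primary, analysed as the between-group difference. The Matsuda index (2.8 units, 80% power at 30 per group) is one example. State whether the powered quantity is the week-8 value or the change from baseline, since the power section does not say.
2. Test the other powered endpoint, here 2-h glucose, next in a fixed sequence at 5%. The article presents the two equally, so the order is for the investigators to choose.
3. Make β-cell function, lipids and body composition secondary, with Holm adjustment.
4. Report within-group changes descriptively.
5. Make gut composition exploratory, with one global community-level test and false-discovery-rate control if taxa are tested individually.

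The cost is fewer endpoints that may be called primary, plus one amendment. The Protocol amendments section requires approval from the funder and the IRB, followed by an update of the registry record. The Trial status section reports 23 participants enrolled as of January 2019, and the Data management section places the final quality checks in year 5, with analysis of each endpoint only afterwards. On that timetable the change can be made without results in hand. Sample size and power for the first endpoint are unchanged.
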